##### Sample Size and Sampling

At baseline, clustered and random sampling will be applied. University students will be enrolled consecutively from randomly selected classes (clusters) at the UCM and UniLicungo. Considering that the baseline survey will serve as identification and enrolment point of participants to the cohort, and the main purpose is to look for differences on determinants and behavior changes between groups (students exposed to the full program and those not exposed); based on a 95% confidence interval, desired confidence interval half-width of 0.15 and Cohen's d of 0.2, a total of 687 participants are needed (32). Assuming a 20% dropout, the final sample size is 824. Hence, the goal is to include 412 participants per university. At each university, ten classes (graduation programs) will be randomly selected, and study participants will be enrolled from selected classes until the sample size is completed starting from the first class randomly identified.

Inclusion criteria

First year university students studying at one of the two universities in faculties located in Beira city.Being aged 16–25 years old.Having residency in Beira city for the entire academic year.

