The health advisor will offer services according to the national guideline (17). He/she will also record the results of STI/HIV screening in the specific form with participant identification number (code). A standard operation procedure (SOP) will be provided to the health advisors. The health advisors will fill in a checklist for each client assisted, they will also be asked to fill in the client record sheet with required data from all clients regardless of being a study participant.

All quantitative data will be processed and analyzed using SPSS (Statistical package for Social Sciences, V. 25), descriptive statistics and proportions will be reported. The baseline data will be compared using t- tests and Chi-square tests. After intervention, data from different universities will be compared using multilevel regression models considering the baseline values and nesting of students within classes. Multilevel regression model analysis has been referred to be an eligible method to analyze data from research with a hierarchical structure, and variables measured at different levels and time-points (35–38). This method enables an assessment of the effects of variables measured at different levels of the hierarchy, for example class, student and repeated points of measure indeed, many benefits has been mentioned (36). The data from the baseline survey will be used to estimate the effect size. Additionally, Cohen's d test will be used to estimate the effect size with 95% confidence interval, relative risk and Odds ratio will be determined to measure the extent to which the intervention affects the (determinants of) behavior.

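### The sample size of 687 (824 with dropout) allows nothing for sampling by class, so the stated half-width of 0.15 for Cohen's d holds only if the intraclass correlation is zero

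*Protocol article*

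**What the plan says.** Under Effect Evaluation, Sample Size and Sampling, the protocol article bases the size on a precision target: "based on a 95% confidence interval, desired confidence interval half-width of 0.15", with a Cohen's d of 0.2. This gives 687 in total. It continues: "Assuming a 20% dropout, the final sample size is 824", and "the goal is to include 412 participants per university".

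The same section makes the class the sampling unit: "University students will be enrolled consecutively from randomly selected classes (clusters) at the UCM and UniLicungo". It then sets the number of classes and the enrolment rule for each university: "ten classes (graduation programs) will be randomly selected, and study participants will be enrolled from selected classes until the sample size is completed", beginning with the first class drawn.

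Under Effect Evaluation, Study Procedure, the universities are compared after the intervention by "multilevel regression models considering the baseline values and nesting of students within classes". Cohen's d is also to be reported with a 95% confidence interval.

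The article states no ICC, no design effect and no class size.

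**The concern.** The sampling and the analysis both treat classes as clusters, but the sample size appears to treat students as independent. Each class lies wholly within one university, so exposure to the full program does not vary within a class. The full class-level design effect therefore falls on the comparison between universities, which is the study's main purpose.

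The half-width is the only precision statement in the plan. Taken at face value, it promises an interval of 0.05 to 0.35 around d = 0.2. With positive correlation within classes the interval is wider, and it may no longer exclude zero.

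The enrolment rule adds a second concern. Ten classes are drawn, but enrolment may finish before all ten have been used. That would leave fewer and larger clusters.

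**Working it through.** **Inputs from the article:** 95% confidence, half-width 0.15, d = 0.2, total 687, dropout 20%, final size 824, 412 per university, 10 classes per university.

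**Assumed, because the article gives no value:** ICC of 0.01, 0.02 and 0.05; where baseline adjustment is considered, a baseline-to-follow-up correlation of 0.5.

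**Step 1: reproduce 687.** For two independent groups of n individuals, half-width = 1.96 × √[(2 + d²/4)/n]. Solving for n:

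n = 1.96² × (2 + 0.2²/4) / 0.15² = 3.8416 × 2.01 / 0.0225 = 343.2 per group, or 686.4 in total, rounded up to 687.

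The match is exact. Any design effect above 1 would have given a larger number.

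**Step 2: number analysed.** 687 × 1.2 = 824.4, stated as 824. Losing 20% of 824 leaves 824 × 0.8 = 659.2, or 329.6 per university. With ICC = 0 the half-width is then 1.96 × √(2.01/329.6) = 0.153.

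**Step 3: add the clustering.** With all 20 classes in use, m = 659.2/20 = 32.96 analysed per class. The design effect is 1 + (m − 1) × ICC = 1 + 31.96 × ICC, and the half-width is 0.153 × √(design effect). With 20 clusters in two groups, a t quantile on 18 df (2.101) is more suitable than 1.96 and widens the result by 2.101/1.96 = 1.072. Baseline adjustment with correlation 0.5 multiplies the half-width by √(1 − 0.5²) = 0.866, which is about 13% narrower.

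| Assumed ICC | Design effect | Half-width, z | Half-width, t (18 df) | z, baseline-adjusted | t, baseline-adjusted |
|---|---|---|---|---|---|
| 0.01 | 1.32 | 0.176 | 0.189 | 0.152 | 0.163 |
| 0.02 | 1.64 | 0.196 | 0.210 | 0.170 | 0.182 |
| 0.05 | 2.60 | 0.247 | 0.264 | 0.214 | 0.229 |

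**Step 4: when an interval around d = 0.2 reaches zero.** This needs a half-width of 0.2.

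- Unadjusted, z: design effect (0.2/0.153)² = 1.71, so ICC = 0.71/31.96 = 0.022.
- Adjusted, z: design effect 1.71/0.75 = 2.28, so ICC = 1.28/31.96 = 0.040.
- With t on 18 df the same steps give about 0.015 unadjusted and 0.031 adjusted.

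**Step 5: the enrolment rule.** Using all ten classes means an average of 412/10 = 41.2 enrolled per class. If the first classes yield more than that, enrolment ends early. As an illustration only, stopping after six classes per university gives m = 659.2/12 = 54.9. At ICC 0.05 the design effect is 1 + 53.9 × 0.05 = 3.70 and the half-width is 0.153 × √3.70 = 0.294 (z), against 0.247 with ten classes.

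**The case against.** **The planned model already handles clustering and baseline.** This is true, and it limits the damage: the analysis itself takes account of class nesting, so the fault lies in the stated precision. Baseline adjustment could also recover most of the loss at a low ICC (0.152 by z at ICC 0.01 with a correlation of 0.5). However, the sample size section claims no such credit, and the formula behind 687 is for an unadjusted d.

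**An article condenses a fuller protocol.** That would excuse a missing ICC. It does not excuse a published total that can be shown to contain no allowance for clustering.

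**The size of the shortfall rests on an assumed ICC.** This stands. Only the direction is certain, for any ICC above 0.

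**Stronger readings that the article does not support.** A reader might infer that the interval will in practice reach or cross zero. It need not: at ICC 0.01, and at 0.02 by the normal quantile, the interval around 0.2 still excludes zero. A reader might also infer that the enrolment rule will leave classes unused. No class sizes are given; if classes yield about 41 participants or fewer, all ten are used and the rule does no harm. Nor is the arithmetic behind 687 wrong: it is correct for a design with independent students, which this is not.

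**Conclusion.** The point holds. The figure of 687 is the independent-individuals answer applied to a class-sampled design, and the unadjusted half-width of 0.15 requires an ICC of 0. For assumed ICCs of 0.01 to 0.05, with 659 analysed in 20 classes, a realistic statement is about 0.18 to 0.25 (z) or 0.19 to 0.26 (t, 18 df). An interval around d = 0.2 may reach zero if the ICC exceeds about 0.02 unadjusted, or about 0.04 with baseline adjustment at a correlation of 0.5; the t quantile lowers both thresholds. The harm from the enrolment rule is conditional on class sizes.

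These figures assume equal class sizes. They also leave out variation between universities: with one university per condition, a class-level design effect cannot cover it, so the half-widths understate the uncertainty about a program effect.

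**What to change.** 1. **Restate the precision and keep 824.** State and justify an ICC with a range. Replace the unqualified 0.15 by the half-width that 824 less 20% dropout delivers in 20 classes, using a t value suited to that number of clusters. If credit is taken for baseline correlation, state the correlation assumed. Add that the figure does not cover variation between the two universities.
2. **Enrol from all ten selected classes per university.** Set a target of about 41 students per class, or enrol in proportion to class size. Where a class is smaller than its target, take all eligible students and make up the shortfall from the other selected classes. This replaces filling up from the first class drawn.

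The cost is a less favourable stated precision and visits to all ten classes, which are selected in any case. No more participants are required.

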Occurrence of STI/HIV	To what extent the prevalence and incidence of Syphilis, HIV and reported general symptoms of STI changed.	Prevalence and incidence of Syphilis/HIV or symptoms of any STI.	Analysis of counseling and testing services records, including test results.

A cohort study applying a quasi-experimental non-equivalent control group design with pre-post approach will be used since the intervention is ongoing and by its nature, the use of a full experimental design is unjustifiable. Students registered for the first year, willing to take part in this study, will fill in the questionnaire at enrollment, post intervention and at follow up. The participants will be encouraged to visit a health advisor to undergo an STIs screening through clinical and testing examination. Considering that the prevalence of STI in general is high among young adults, and the primary outcome of the intervention is (determinants of) behavior change, all students, no matter their STI/HIV state, will be enrolled in the cohort and followed-up for 6 months. Students enrolled at UCM will be exposed to the full program, and students from UniLicungo will only receive information from research team and teachers to visit STI counseling and testing office.

The main aims of the cohort are: To analyze changes in behavior and individual-level determinants that in turn influence unprotected sex behavior and use of STI/HIV screening services among university students in Beira city after exposure to the intervention, as well as to monitor cyclical transmission of STIs including HIV among first year university students in Beira at 3 and 6 months after setting up the cohort. During the follow-up period there will be regular consultations, every 3 months for STIs/HIV screening and questionnaire self-filling. Treatment will be offered at the health center to students that are diagnosed with an STI, and the participant will not be withdrawn from the cohort.

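### The enrolment target of 824 does not absorb the stated 20% dropout: about 659 would complete, against the 687 the plan says it needs

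*Protocol article*

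**What the plan says.** Under Effect Evaluation, Sample Size and Sampling, the protocol article bases the sample size on precision: "based on a 95% confidence interval, desired confidence interval half-width of 0.15 and Cohen's d of 0.2, a total of 687 participants are needed". It then adds an allowance for loss: "Assuming a 20% dropout, the final sample size is 824". The total is split equally: "the goal is to include 412 participants per university". It prints no dropout formula and states no other adjustment between 687 and 824.

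The same section treats the baseline survey as the point of enrolment into the cohort. It has students recruited from the selected classes until the target number is reached. The Effect Evaluation section says that all students, whatever their infection status, "will be enrolled in the cohort and followed-up for 6 months".

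**The concern.** A dropout allowance should leave the required number after the assumed loss. Dropout is a fraction of those enrolled, so the required number has to be divided by the fraction expected to remain. Multiplying it by one plus the dropout rate gives too small a figure. The published 824 looks like the result of that multiplication.

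Two things are at stake. First, the sample size statement does not deliver its own requirement under its own assumption, and this is so before clustering by class is considered. Second, 824 is the operational end of recruitment. Enrolment happens at the baseline survey, so a shortfall discovered at 6 months cannot be made up with students who have baseline data.

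**Working it through.** **Inputs, all from Sample Size and Sampling:** 95% confidence interval, target half-width 0.15, Cohen's d = 0.2, required total 687, dropout 20%, final total 824, 412 per university.

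**Step 1. Reproduce 687.** For two equal groups with total N, the large-sample half-width of the interval for d is

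1.96 × √(4/N + d²/(2N)) = 1.96 × √(4.02/N) at d = 0.2.

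- N = 686 gives 0.15004, just above the target.
- N = 687 gives 0.14993, which meets it.

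So 687 is the smallest total that meets the target. An interval based on the noncentral t distribution gives the same N. The base figure is therefore correct for independent observations, and it holds no slack to absorb a later shortfall.

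**Step 2. Reproduce 824.**

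| Rule | Calculation | Result |
|---|---|---|
| Multiply by 1 + dropout | 687 × 1.2 | 824.4, matches 824 |
| Divide by 1 − dropout | 687 / 0.8 | 858.75, so 859 |

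Only the first rule gives the printed figure. The gap is 859 − 824 = 35 enrolled, or 36 with equal groups (2 × 430 = 860).

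**Step 3. Apply the stated dropout to 824.**

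- Completers: 824 × 0.8 = 659.2, about 659 (412 × 0.8 = 329.6 per university).
- Shortfall: 687 − 659 = 28, which is 28/687 = 4.1% of the requirement.
- Dropout that 824 does cover: 1 − 687/824 = 16.6%.

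**Step 4. Effect on precision.** With 659 completers the half-width is 1.96 × √(4.02/659) = 0.1531, against 0.1499 at 687. The interval is about 2% wider.

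**Step 5. Check the correction.** 860 × 0.8 = 688, which is at least 687.

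**The case against.** The arithmetic is not in dispute. The case on the other side is that it hardly matters and that some of the wording could overstate it.

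- **Size.** The half-width moves by about 0.003. The 0.15 is a desired precision and not a decision rule, the 20% is a round assumption without a source, and no hypothesis or test in the plan changes. This stands, and it makes the point a correction to a stated figure rather than a threat to the study.
- **Partial data.** Questionnaires are planned at enrolment, 3 months and 6 months, and the Study Procedure section plans multilevel models that can take repeated measurements. A student seen at 3 months but lost by 6 months may still contribute. This stands too: 659 is best read as the number completing, and 28 short is the worst case for the analysis.
- **A different analysis.** The half-width formula is unadjusted and assumes independent students, while the planned models adjust for baseline and for class. As an illustration, an assumed baseline–outcome correlation of 0.20 would by itself offset a 4% loss of sample (1 − 0.20² = 0.96). Clustering would act in the other direction, possibly more strongly. So 0.153 is not a forecast of the precision the study will achieve. It shows only what the plan's own calculation gives.
- **Inferred formula.** The article does not print the multiplication by 1.2. That is correct, but the conclusion does not depend on it: 80% of 824 is about 659 however 824 was reached.

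Reading the 20% as a share of 687 instead of a share of those enrolled does not help. It would mean losing 137 of 824, which is 16.6% dropout. Nor can 687 be meant for baseline only. The stated purpose is to compare change between groups, and a baseline-only requirement would need no dropout allowance. None of these arguments makes 687, 20% and 824 consistent.

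**Conclusion.** The concern holds. The enrolment target falls short of the plan's own requirement: 824 enrolled with 20% loss leaves about 659 completers against 687, and 824 covers 16.6% dropout. The matching enrolment figure is 859, or 860 for equal groups.

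The consequence is modest: 35 or 36 too few enrolled, 28 too few completing, and a half-width of about 0.153 instead of 0.150. The counts rest only on the printed figures and on dropout being a share of those enrolled. The half-width also assumes equal groups, independent observations, an unadjusted comparison and no contribution from students who drop out. Whether 687 is itself enough once students are nested in classes is a separate question, which this point does not address.

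**What to change.** Correct the one sentence in Sample Size and Sampling, in either of two ways:

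1. **Keep 824 (412 per university) and restate what it provides.** Say that it allows for 16.6% dropout, or that at 20% dropout about 659 participants complete, with a half-width of about 0.153, unadjusted and before any design effect. This needs no extra enrolment. The cost is a slightly less favourable stated precision.
2. **Raise the target to 860 (430 per university)** if the selected classes can supply them. This keeps both the 0.15 target and the 20% assumption, at a cost of 36 more students, 18 per university.

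In either case, give the formula used for the allowance so that a reader can reproduce the figure.

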##### Study Procedure

Data collection will be performed by three data collectors after being trained in a 2-day session. The training will focus on study aims, how to obtain informed consent, how to approach the participants and how to distribute and collect the questionnaires. The data will be collected through a self-administered structured questionnaire (see Supplementary File, Appendix 3) with closed-ended questions in Portuguese, the official language of Mozambique. The questionnaire is developed based on the change objectives (see matrices in Supplementary File), using Likert-type response scales (33) and guided by recommendations of Fishbein & Ajzen (34). One or two days before data collection, courses' coordinator of each selected class will explain about the study and invite students to take part. Confidentiality will be ensured, and codes will be used to identify each participant's questionnaire including the study participant's identification card.

Informed consent will be obtained collectively before questionnaire distribution to the class though each candidate will freely decide and sign the consent form. The data collection process will take place in classrooms. The same questionnaire will be administrated to the study participants three times (time 0 at enrolment visit; time one after 3 months of program implementation and time 2 6 months after). At the time one and two, participants will be asked to respond only to questions regarding intersexual relationship (section 2) and questions addressing behavioral outcome 1 and 2 (section 3 and 4, respectively).

During the time of filling in questionnaires, students will not be allowed to chat or to look at classmates' answers. Thus, in case of doubt, students will be advised to ask the data collector for clarification. After a given time for completing, the data collector will recollect the questionnaires, give a study participant identification card, and recommend her/him to visit the health advisor office for STIs counseling and screening within the following days.

The health advisor will offer services according to the national guideline (17). He/she will also record the results of STI/HIV screening in the specific form with participant identification number (code). A standard operation procedure (SOP) will be provided to the health advisors. The health advisors will fill in a checklist for each client assisted, they will also be asked to fill in the client record sheet with required data from all clients regardless of being a study participant.

All quantitative data will be processed and analyzed using SPSS (Statistical package for Social Sciences, V. 25), descriptive statistics and proportions will be reported. The baseline data will be compared using t- tests and Chi-square tests. After intervention, data from different universities will be compared using multilevel regression models considering the baseline values and nesting of students within classes. Multilevel regression model analysis has been referred to be an eligible method to analyze data from research with a hierarchical structure, and variables measured at different levels and time-points (35–38). This method enables an assessment of the effects of variables measured at different levels of the hierarchy, for example class, student and repeated points of measure indeed, many benefits has been mentioned (36). The data from the baseline survey will be used to estimate the effect size. Additionally, Cohen's d test will be used to estimate the effect size with 95% confidence interval, relative risk and Odds ratio will be determined to measure the extent to which the intervention affects the (determinants of) behavior.

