##### Sample Size and Sampling for the Process Evaluation

All teachers involved in teaching life skills are included, health advisors and a sample of activists will be invited to take part in the study. Additionally, A sample of first year students from the Faculty of Health Sciences and the Faculty of Economy and Management, both at the UCM, will be systematically selected through a stratified random sampling procedure strategy from the cohort's participants list within faculty and gender groups, as well as consideration of a number of interviews to achieve saturation, which is expected to range between 6 and 12 per gender and per faculty (23–25). The same procedure will be applied to select participant from the activists' groups at both Faculties of the UCM.

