The program described in this manuscript, which we aim to evaluate, is already in its full implementation, meaning that it might be an unjustifiable and unfeasible procedure to apply a full experimental study design with random allocation to intervention and control group, which would imply excluding some classes or students from the intervention at UCM, while they share the same environment and policies. Hence to have a comparison group, similar in age and level of education, a quasi-experimental design assigning students from another university as comparison group is a rational and acceptable approach to evaluate the effect of the intervention aiming to change (determinants of) behavior with limited biases.

Traditionally, randomized controlled trials have been seen as gold standard for generating casual evidence in health sciences field, especially when it comes to warrant inclusion criteria in systematic reviews and meta-analysis (45, 46). However, for this study, a quasi-experimental non-equivalent control group design was chosen, since the design combines some of the advantages of the full experimental designs with those of no experimental studies, offering distinct advantages compared to randomized controlled trials. Particularly, the design limits some of the threats to external validity that can be seen as a weakness of the full experimental designs (45).

Although quasi-experimental studies have some advantages compared to other designs, it is recognized that they will only result in acceptable or valid inferences when conducted in a way that meet certain assumptions (45). They are recommended when the study pretends to evaluate complex interventions for instance health behavior change (46–48), which is our case. The design will enable to generate outcomes with high external validity since the data will be collected under natural conditions. Admittedly, quasi-experimental study designs as described above, are challenged by some limitations such as lack of individual participant randomization to each arm and need for advanced statistical analysis. The results from this study can be influenced by several pitfalls for instance, selection bias, maturation bias, Hawthorne effect (observation effect), historical bias, regression to mean, ascertainment bias and reporting bias (49–51). Most of these biases will be controlled by using the control group pre-post approach.

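### The between-university outcome model names only baseline values and class nesting, so student-mix differences that affect change over 6 months can be read as a programme effect

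*Protocol article*

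**What the plan says.** The Effect Evaluation section sets the design: "A cohort study applying a quasi-experimental non-equivalent control group design with pre-post approach will be used". One university receives the full programme and the other serves as control.

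The analysis paragraph (Effect Evaluation, Study Procedure) describes two steps. First, "The baseline data will be compared using t- tests and Chi-square tests". Second, after the intervention, the universities are compared with multilevel regression models "considering the baseline values and nesting of students within classes". No gender, age, relationship or field-of-study term is named, and nothing links the baseline tests to the model.

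The Discussion argues comparability in these terms: "Hence to have a comparison group, similar in age and level of education". It lists several threats, selection and maturation bias among them, and concludes: "Most of these biases will be controlled by using the control group pre-post approach".

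Three other statements bear on the point:
- Sample Size and Sampling (Effect Evaluation): ten classes, which are degree programmes, are drawn at random at each university and filled in order until the target is met. Both arms are limited to first-year students aged 16 to 25 who live in Beira for the academic year.
- Sample Size and Sampling for the Process Evaluation: students at the programme university are sampled from the cohort's "participants list within faculty and gender groups".
- Study Procedure (Effect Evaluation): section 2 of the questionnaire covers relationships and is asked at all three time points.

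**The concern.** Without randomisation, the adjustment set carries much of the weight of the inference. The two named elements do limited work here. Class nesting accounts for correlation among students in the same class. Classes sit inside universities, so nesting does not balance the two student bodies. Baseline adjustment handles a difference in starting level. It does not handle two groups of different composition that would have moved at different rates over the first university year anyway, which is selection interacting with maturation.

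The plan leaves room for the mix to differ. Degree programmes are drawn separately at each university, with no matching described, and filled in sequence. The composition of each arm therefore depends on which programmes come up first. The authors treat gender and faculty as relevant when they stratify the process sample, but the effect model names neither.

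At stake is the main contrast. A residual difference of this kind could inflate or mask a programme effect, and the Discussion as worded would lead readers to think that the design had dealt with it.

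**Working it through.** **1. The plan's own scale.** Inputs from Sample Size and Sampling (Effect Evaluation): 95% confidence, half-width 0.15, d = 0.2.

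- n per group = (1.96/0.15)² × (2 + d²/4) = 170.74 × 2.01 = 343.18
- Total = 2 × 343.18 = 686.4, rounded up to 687, as stated
- 687 × 1.2 = 824.4, which matches the stated 824

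The sample size is not in dispute here. It supplies the yardstick (d = 0.2) and the implied standard error, 0.15/1.96 = 0.0765.

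**2. Residual bias after baseline adjustment.**

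Bias (SD) = (difference between universities in the share of students with a characteristic) × (effect of that characteristic on follow-up, given baseline)

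The documents give neither factor, so both are assumptions.

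| Mix difference | Effect 0 | Effect 0.2 SD | Effect 0.3 SD | Effect 0.4 SD |
|---|---|---|---|---|
| 10 points | 0 | 0.02 | 0.03 | 0.04 |
| 20 points | 0 | 0.04 | 0.06 | 0.08 |
| 30 points | 0 | 0.06 | 0.09 | 0.12 |

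As a share of d = 0.2, the range is 0% to 60% (0.12/0.2). The middle case, 20 points and 0.3 SD, gives 0.06/0.2 = 30%.

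**3. Effect on false positives.** With SE = 0.0765 and ignoring clustering, a bias of 0.06 raises the two-sided type I error from 5% to about 12%, and a bias of 0.12 raises it to about 35%. Clustering would widen the SE and lower these percentages, but the bias would stay the same.

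**4. Simulation check.** Settings: 343 per arm, true programme effect 0, baseline to follow-up correlation 0.5, one binary covariate with a 0.3 SD effect at baseline, 2,000 runs, no clustering. The effect given baseline is the follow-up effect minus 0.5 × 0.3 = 0.15.

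| Mix difference | Covariate effect at follow-up | Effect given baseline | Baseline-only model: bias / type I error | Covariate added: bias / type I error |
|---|---|---|---|---|
| 20 points | 0.15 SD | 0 | about 0 / 5% | about 0 / 5% |
| 20 points | 0.30 SD | 0.15 | 0.03 / 7% | about 0 / 5% |
| 20 points | 0.50 SD | 0.35 | 0.07 / 18% | about 0 / 5% |

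The first row matters as much as the last. Where the covariate acts only through the baseline outcome, the model as written is unbiased. Bias appears only when the covariate also drives change.

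**The case against.** The strongest reply is that the article never says the model adjusts only for these two things. The phrase baseline values is plural and undefined. The same paragraph says that multilevel models can assess variables at class and student level, so student covariates fit the stated method. A covariate list is also something a condensed article may leave to a fuller document. This stands in part: a reader might infer that covariates are excluded, and the text does not say so. What keeps the point alive is the Discussion, which makes a positive claim that the pre-post control approach handles most of the listed biases. For selection and maturation bias that is too strong, whatever an analysis plan may add.

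Second, some confounding is already limited. Both arms share the year, age and residency restrictions. Condom use and use of testing services are themselves outcomes with time-0 values, which plausibly carry much of the information on earlier behaviour. This also stands, and it is why the lower end of the range is zero.

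Third, a reader might infer that every useful covariate is already in hand. The documents support this only in part. Age is an eligibility criterion at both universities, and section 2 covers relationships. The gender list is mentioned only for the programme university. Collection of gender at the control university, and of sexual experience and earlier testing at either, is inferred, because the questionnaire appendix is not shown.

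**Conclusion.** The point holds in a limited form. The stated model leaves unadjusted any student-mix difference that affects change beyond what the baseline outcome carries, and the Discussion credits the design with more control than it gives. The possible bias is 0 to 0.12 SD, or 0% to 60% of the planned d of 0.2. That range rests wholly on assumed mix differences of 10 to 30 points and assumed effects of 0 to 0.4 SD.

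Two stronger conclusions are tempting and not supported. One is that the result will be biased: nothing in the documents shows that the universities differ in gender or relationship mix, or that these variables drive change over 6 months. The other is that covariate adjustment would make the contrast a clean estimate of the programme effect. With one university per arm, other university-level differences cannot be separated from the programme by any student-level model.

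This is a change worth making, not a fatal flaw.

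**What to change.** - **Model.** In the multilevel models of the analysis paragraph (Effect Evaluation, Study Procedure), add time-0 gender, age and relationship status (section 2) as fixed student-level covariates. Add sexual experience and earlier STI/HIV testing if the questionnaire records them. Confirm that gender is recorded at both universities. Use time-0 values only, because later relationship answers could themselves be affected by the programme.
- **Selection of covariates.** Fix the list in advance. Do not let the baseline t-tests or chi-square tests decide what enters.
- **Reporting.** Show the estimates with and without these covariates side by side.
- **Discussion.** Reword the sentence on bias control to say that the pre-post control design with covariate adjustment reduces selection bias but does not remove it. State that, with one university per arm, other university-level differences cannot be separated from the programme.

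The cost is a little more analysis work and a few degrees of freedom. The sample size does not change. No new data are needed for the three core covariates, provided that gender is recorded at the control university.
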